### STAGE 3: adapt the implementation strategies

This stage will involve the review of and reflection on each implementation strategy, according to the defined method of evaluation as identified in stage one and the quantitative and qualitative pilot programme results from stage two. Reflecting and evaluating also lends itself to the ‘process’ construct under the CFIR, with a specific focus on implementation efforts, accompanied with personal and team debriefing about progress and experience [33]. Thus, the steering committee will decide on appropriate and realistic adaptations to be made to the implementation strategies based on the pilot findings. These strategies will then be used to launch the national GLA:D® Ireland programme for hip and knee OA and incorporated into future training workshops for physiotherapists. Strategies will be re-evaluated during the review of GLA:D® Ireland implementation annually and adapted where necessary.

#### Evaluation of effectiveness

An electronic GLA:D® Ireland registry will collect participant consent and all therapist- and patient-reported data from baseline, 3- and 12-months follow-up. The secure REDCap™ software platform will be used to build, collect and manage all data related to the registry and research project. An evaluation of programme effectiveness relating to self-reported and measured outcomes such as pain, joint symptoms, quality of life and functional capacity (outcomes collected presented in Additional file 5) will be performed at each annual review. Effectiveness outcomes, using a pre-post design, will be analysed to evaluate change scores (baseline to 3- or 12-month follow-up) with 95% confidence intervals to determine significance (α = 0.05) and clinical significance where a published value exists. If appropriate, a mixed-effects model will be used with patient as a random effect and time as a fixed effect. Sensitivity analyses will be conducted to determine differences in results related to site of pain (knee/hip), history of joint replacement and private or public setting. IBM SPSS® Statistics 26 will be used to perform all statistical analyses.

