**Methods:**

Using a type III hybrid implementation-effectiveness design, a participatory, dynamic and iterative process will be used to tailor and evaluate multi-level implementation strategies using the following stages: 1) Co-design the implementation strategies with key stakeholders using best evidence, a theory-driven implementation framework (Consolidated Framework for Implementation Research), local context and expert consensus; 2) Pilot and evaluate the implementation strategies by training physiotherapists to deliver the evidence-based Good Life with osteoArthritis Denmark (GLA:D®) education and exercise programme using the implementation strategies, and conduct a mixed-methods process evaluation; 3) Adapt the implementation strategies based on implementation process evaluation indicators from stage two. The adapted strategies will be used for scale-up and sustainability in subsequent GLA:D® Ireland training programmes that will be rolled out nationally. Evaluation of effectiveness on patient and cost outcomes will continue up to 12 months post-programme delivery, using an online patient registry and pre-post design.

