#### GLA:D® pilot programme delivery

GLA:D-trained physiotherapists (*n* = 8–10) will make use of existing or new referral sources to invite people with hip or knee OA to take part in the GLA:D® programme, as applicable for each setting. These sources include but are not restricted to clinic or orthopaedic waitlist, GP or other healthcare professional referral and self-referral. Eligible participants will have ‘joint problems from knee and/or hip that have resulted in contact with the health care system’. Exclusion criteria include non-OA cause of symptoms, e.g., tumour; inflammatory joint disease, or sequelae after hip fracture; other symptoms that are more pronounced than the OA problems, e.g., chronic, generalised pain, or fibromyalgia, acute knee trauma in the past 6 months or inability to understand the English language. The GLA:D® programme will comprise two to three education sessions and 12 (twice weekly) group neuromuscular exercise sessions as described in detail previously [15]. All group sessions will be supervised by a physiotherapist and can be delivered in a face-to-face or online format, as per clinician/patient preference and capability. Participants are encouraged to continue being physically active and to exercise, either with their physiotherapist or in their local community, to sustain the effects from the treatment in the long term.

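### Neither the change-score confidence intervals nor the optional mixed model allows for correlation of change among patients treated in the same group or clinic

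*Protocol article*

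**What the plan says.** The analysis is set out in the protocol article, Stage 3, Evaluation of effectiveness. Change from baseline to 3 or 12 months is assessed "with 95% confidence intervals to determine significance (α = 0.05"). A model is then offered as an option: "If appropriate, a mixed-effects model will be used with patient as a random effect and time as a fixed effect". Sensitivity analyses look for differences by site of pain, "history of joint replacement and private or public setting". The evaluation uses registry data and "will be performed at each annual review".

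Delivery is described in Stage 2, GLA:D® pilot programme delivery. Participants receive "two to three education sessions and 12 (twice weekly) group neuromuscular exercise sessions", and "All group sessions will be supervised by a physiotherapist". Referral source follows the setting, and sessions may be online or face-to-face. Training of physiotherapists says that the first providers come from different regions, from small and large private clinics, and from public primary care and orthopaedic hospitals.

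No part of the article mentions correlation among patients who share a group, a physiotherapist or a clinic.

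**The concern.** Patients who share a supervising physiotherapist, an exercise group, a referral route and a delivery format may improve by similar amounts. The protocol itself expects delivery to vary, because its fidelity question asks providers what they changed. A patient random effect deals only with repeated measurements on one person. It leaves the changes of two patients in the same clinic independent, as does an ordinary interval for a mean change.

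If that independence fails, the standard errors are too small and the intervals cover less often than 95%. Private or public setting is essentially an attribute of the clinic, so a patient-level comparison could mistake ordinary clinic-to-clinic variation for an effect of setting.

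The results have a use. The Discussion plans annual public reports, and intends to use patient outcomes after one year to argue for funding with the Department of Health and the Health Service Executive.

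**Working it through.** **Inputs from the document.** α = 0.05 with 95% intervals (two-sided implied); patient is the only random effect named; delivery is in supervised groups. The article gives no sample size, standard deviation, intraclass correlation (ICC) or number of patients per clinic, so there is no design figure to reproduce.

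**Assumptions.** ICC of the change score: 0, 0.01, 0.05 or 0.10. Patients per clinic (m): 10 or 30, with clinics of equal size.

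**Formulas.**
- Design effect: DE = 1 + (m − 1) × ICC.
- Factor by which the interval should be widened: √DE.
- Actual type I error of the nominal 5% test: 2 × [1 − Φ(1.96/√DE)].

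Example: m = 30 and ICC = 0.05 give DE = 1 + 29 × 0.05 = 2.45, √DE = 1.57, 1.96/1.565 = 1.25, and a type I error of 21.1%.

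| m | ICC | DE | √DE | Type I error | Coverage |
|---|---|---|---|---|---|
| 10 | 0 | 1.00 | 1.00 | 5.0% | 95.0% |
| 10 | 0.01 | 1.09 | 1.04 | 6.0% | 94.0% |
| 10 | 0.05 | 1.45 | 1.20 | 10.4% | 89.6% |
| 10 | 0.10 | 1.90 | 1.38 | 15.5% | 84.5% |
| 30 | 0 | 1.00 | 1.00 | 5.0% | 95.0% |
| 30 | 0.01 | 1.29 | 1.14 | 8.4% | 91.6% |
| 30 | 0.05 | 2.45 | 1.57 | 21.1% | 78.9% |
| 30 | 0.10 | 3.90 | 1.97 | 32.1% | 67.9% |

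**Does the number of clinics matter?** In simulation (10,000 replicates per scenario, m = 10, ICC = 0.05) the patient-level test rejected a true null in 10.5%, 10.6% and 10.1% of runs with 8, 10 and 40 clinics. The error depends on ICC and clinic size, not on how many clinics there are. A t-test on clinic means held 4.7% to 5.3% in every scenario.

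**Does a difference in level alone matter?** No. When clinics differed in level but not in change (9 clinics, m = 10, 4,000 replicates), the patient-level test rejected in 5.0% of runs, because the level cancels from the difference. For the same reason a random site intercept alone would not correct the time effect.

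**Private/public contrast.** If every clinic belongs to one setting and clinics are of equal size, the variance of each setting's mean is multiplied by the same DE, and so is the variance of their difference. The formula therefore gives the same error rates for a patient-level test of setting. This is from the formula only, not simulated.

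**The case against.** The case against a strong claim has four parts, and much of it stands.

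- **The consequence is conditional.** A reader might infer that the intervals are certainly too narrow for every outcome. The document does not support that. Without correlation of change the test keeps its 5%, and at ICC 0.01 with 10 patients per clinic it is about 6%.
- **The small pilot count is not the cause.** A reader might link the model to the pilot: "GLA:D-trained physiotherapists (*n* = 8–10) will make use of existing or new referral sources". That count belongs to Stage 2. The model serves the annual registry evaluation, with "subsequent GLA:D® Ireland training programmes that will be rolled out nationally", and no number of providers or clinics is given for that dataset. The count affects the degrees of freedom available to a remedy, not the inflation.
- **The model is optional, and the article is condensed.** It does not say that patient is the only random effect, and a fuller plan may say more. This does not remove the point. The article chooses to state one structure, and the analysis it sets without condition, the change-score interval, has the same gap.
- **The setting comparison is not specified.** A reader might infer that private and public patients will be tested as independent units. The article states neither a test nor a unit of analysis for these sensitivity analyses, so this is an exposure and not a stated error.

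On weight, the objection is right that no primary conclusion depends on this. The Discussion describes effectiveness as monitoring alongside primary implementation outcomes, which are analysed descriptively. It also acknowledges the lack of a comparison group.

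**Conclusion.** The point holds in conditional form. The stated analysis ignores a level of clustering that is built into the way the programme is delivered, in both the change-score intervals and the optional model. If change correlates within clinic, the intervals should be 1.04 to 1.97 times as wide and the nominal 5% test runs at about 6% to 32%. Those ranges rest on the assumed ICCs and clinic sizes, not on figures in the protocol. National roll-out does not remove the problem, and more patients per clinic makes it worse. The omission itself is certain; its size is not.

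Severity is moderate. The uncontrolled pre-post design limits what can be concluded more than this does, and the analysis can be corrected without touching recruitment, delivery or data collection.

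**What to change.** Amend both analyses under Evaluation of effectiveness, not the mixed model alone. Suggested wording:

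*Confidence intervals for change scores will allow for clustering by site (or physiotherapist), using cluster-robust standard errors. Where a mixed model is used, it will include time as a fixed effect, patient as a random effect, and a site-by-time random effect. A small-sample correction will be applied while sites are few. Differences between private and public settings will be judged against between-site variation.*

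Name the clustering level explicitly. Robust standard errors clustered by site also cover groups and physiotherapists nested within that site.

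**Cost.**
- A few sentences of wording. The site identifier should already be held, since Table 2 has the registry count sites trained and sites implementing.
- Wider intervals, possibly much wider in large clinics. With an assumed 50 patients per clinic and ICC 0.05, DE = 1 + 49 × 0.05 = 3.45 and the factor is √3.45 = 1.86. With a t reference on 8 degrees of freedom (nine clinics) it is about 1.86 × 2.306/1.96 = 2.2.
- With few sites the site-by-time variance may be unstable or estimated as zero. The fallback is an analysis of clinic-level summaries with its weighting stated. Weighting clinics equally answers a different question from weighting patients equally when clinic sizes differ, and missing 12-month data are handled differently, so this is not an exact substitute.

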Dissemination activities arising from the results of this research will be co-planned and reviewed by the steering committee throughout the project. Annual reports, summarising evaluations on the effectiveness of the programme will be produced with accessible, lay terminology and infographics, and shared with clinicians and participants of the programme. Ensuring open access, these reports will also be available for free download on the GLA:D® Ireland website [47]. Sustainment of the GLA:D® Ireland initiative beyond the duration of project funding is one of the primary implementation indicators and will be addressed and tailored in implementation strategy design. The very nature of the implementation-effectiveness research design in this project will work to establish an evidence-based intervention within community healthcare settings. Nonetheless, it is critical that efforts to embed and sustain this initiative long-term are applied, through identification of the supports and processes required at micro, macro and meso levels. There is a clear need to identify and describe factors that affect sustainment outcomes in the field of implementation science, and a lack of evidence supporting discrete sustainment strategies for evidence-based interventions [48].

This research is limited by the pre-post design used to evaluate effectiveness of the intervention, without a comparative group. Since there are 100+ conclusive trials already completed in the area of exercise effectiveness for OA, the pre-post design was considered sufficient for the pragmatic monitoring of health outcomes in practice, alongside primary outcomes of implementation. This research may be subject to bias arising from the specific backgrounds and experiences of the researcher and steering committee members it is acknowledged, for example, that different group members may have prioritised or interpreted strategies and results in a different manner. Results of this research are also limited by the lack of available health administrative data to track healthcare usage in Ireland. However, using self-report, we can track use across private and public health services in this manner, that may not be feasible using health administrative data alone. This is important data to capture within a complex, two-tier system of care.

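### If the optional mixed model is fitted as described, it gives the 3- and 12-month changes one common standard error, which can miscalibrate the intervals in a direction the documents do not determine

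*Protocol article*

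**What the plan says.** All of this is in the protocol article, Stage 3, Evaluation of effectiveness. The registry collects "therapist- and patient-reported data from baseline, 3- and 12-months follow-up". The firm analysis is of "change scores (baseline to 3- or 12-month follow-up) with 95% confidence intervals", and these intervals are used "with 95% confidence intervals to determine significance" at a level of 0.05.

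The next sentence adds a conditional analysis, to apply only where appropriate: "a mixed-effects model will be used with patient as a random effect and time as a fixed effect". The article names no random slope, residual covariance or robust standard error. It does not say when the model would be appropriate. It gives no standard deviation or between-visit correlation for any effectiveness outcome.

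**The concern.** A random patient intercept with independent, equal-variance residuals is a compound-symmetry model: every visit has the same variance and every pair of visits the same correlation. With complete data, the model therefore cannot give the 3-month change a different precision from the 12-month change. The visits are 3, 9 and 12 months apart. Correlation that falls with lag, or spread that changes after the programme, would break that structure.

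Two things are at stake. The first is the coverage of any interval taken from this model. The 12-month interval matters most, because the Discussion intends one-year patient outcomes to support the case for funding. The second is the 12-month estimate itself when some 12-month scores are missing, because the assumed covariance decides how much weight the 3-month score carries for patients without a 12-month score.

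**Working it through.** **Plan's own figure.** There is none to reproduce: the article states no sample size, standard deviation or correlation for these outcomes. Every covariance below is an assumption.

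**Formulas.** Let s_j be the standard deviation at visit j and r_jk the correlation between visits j and k, with 0, 1 and 2 for baseline, 3 and 12 months.

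- True variance of a change: D_jk = s_j² + s_k² − 2·r_jk·s_j·s_k.
- The random-intercept model with complete data uses one variance for every change: V = (D01 + D02 + D12)/3.
- Ratio of model standard error to true standard error: √(V/D_jk).
- Large-sample coverage of a nominal 95% interval: 2Φ(1.96·√(V/D_jk)) − 1.

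**Worked example.** Assume standard deviations 20, 22, 25 and correlations 0.55 (0-3 months), 0.40 (0-12), 0.60 (3-12).

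- D01 = 400 + 484 − 2(0.55)(20)(22) = 400
- D02 = 400 + 625 − 2(0.40)(20)(25) = 625
- D12 = 484 + 625 − 2(0.60)(22)(25) = 449
- V = 1474/3 = 491.3, so the model's standard deviation of change is 22.2, against true values of 20.0 (3 months) and 25.0 (12 months).
- 3 months: ratio 1.108, coverage 97.0%. 12 months: ratio 0.887, coverage 91.8%.

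**Other assumed patterns** (equal standard deviations unless stated):

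| r01 / r02 / r12 | 3-month ratio (coverage) | 12-month ratio (coverage) |
|---|---|---|
| .55 / .45 / .50 | 1.05 (96.1%) | 0.95 (93.8%) |
| .60 / .40 / .50 | 1.12 (97.2%) | 0.91 (92.6%) |
| .70 / .40 / .50 | 1.25 (98.6%) | 0.88 (91.6%) |
| 0.95 per month of lag | 1.51 (99.7%) | 0.84 (90.0%) |
| .50 / .50 / .50 | 1.00 (95.0%) | 1.00 (95.0%) |
| .50 / .45 / .65 | 0.97 (94.2%) | 0.92 (92.9%) |
| .50 / .50 / .65 | 0.95 (93.7%) | 0.95 (93.7%) |
| .40 / .50 / .50 | 0.94 (93.5%) | 1.03 (95.7%) |
| all .50, SDs 1 / 1.2 / 1.0 | 0.97 (94.2%) | 1.08 (96.5%) |

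The first four rows have correlation falling from the 3-month to the 12-month lag: too wide at 3 months, too narrow at 12. The fifth shows no error. In the sixth and seventh the two post-programme visits resemble each other more than either resembles baseline, and both intervals are too narrow. The last two rows reverse the direction.

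**Check by fitting.** A random-intercept fit to 2,000 simulated patients with correlations .60/.40/.50 gave a standard error of 0.0223 for both changes. The paired standard errors were 0.0199 (3 months) and 0.0239 (12 months).

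**Missing 12-month scores.** Assume a true 12-month change of −10 and about 36% missing at 12 months, more often after a worse 3-month score.

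| Assumed covariance | Random intercept | Unstructured | Paired completers |
|---|---|---|---|
| SDs 20/22/25; .55/.40/.60 | −11.1 | −10.0 | −11.2 |
| Equal SDs; .50/.45/.65 | −10.8 | −10.0 | −10.9 |
| Equal SDs; .60/.40/.50 | −9.7 | −10.0 | −9.4 |

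Under true compound symmetry the random-intercept estimate was unbiased. The size of the shift depends on the missingness assumed: repeat simulations gave about −10.9 or −10.6 against the same true −10.

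**The case against.** Four points can be made for the plan.

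1. The model is optional. The 95% intervals and the 0.05 level are attached to the preceding, unconditional change-score sentence. An interval from each visit's own paired differences uses that visit's own change variance and escapes the standard-error problem. This stands, so it cannot be said that the plan's significance decisions rest on the mixed model.

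2. A reader might infer that 12-month intervals will be too narrow and 3-month intervals too wide. The documents do not support that. They give no variances or correlations, and the table shows no error, both too narrow, and the reverse. Nor is unequal spacing an error in itself, since compound symmetry can hold at any spacing.

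3. The sentence does not exclude a residual covariance, and a condensed article may leave that to a fuller plan. This stands in part: the point applies only if the model is fitted as worded. But the article does name a specific random structure, and an analyst who follows it would fit the compound-symmetry model.

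4. The effectiveness analysis is monitoring alongside primary implementation outcomes, and the article admits it is "limited by the pre-post design used to evaluate effectiveness of the intervention, without a comparative group". This stands and limits the severity. No conclusion has been shown to change.

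**Conclusion.** The concern holds conditionally. If the mixed model is used, and fitted as described with independent equal-variance residuals, the two changes from baseline share one standard error when data are complete. That is correct only if the two changes have equal variance and that variance equals the average of the three pairwise change variances, as under compound symmetry.

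Across the assumed equal-variance patterns with correlations between .4 and .7, coverage ran from 91.6% to 98.6%. The steep decay of 0.95 per month gave 90.0% and 99.7%. The direction cannot be settled from the documents.

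The 12-month estimate can also be biased when missingness depends on the 3-month score: about 0.3 to 1.1 points on a true change of 10 in the examples above. This rests on an assumed amount and mechanism of missingness, neither of which the article gives. Paired completer changes were biased in the same examples, so they avoid the standard-error problem but not this one. Severity is minor to moderate.

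**What to change.** Where the mixed model is used, fit visit (0, 3, 12 months) as a categorical fixed effect with an unstructured within-patient covariance over the three visits. This replaces the patient random intercept; it is not added to it. Report the 3- and 12-month changes as contrasts from that model with their 95% intervals.

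The cost is one line of specification and four more covariance parameters (six instead of two), which is small for a national registry. The model can be fitted in the software the article names. It gives each change its own variance whichever way the error would have run. In the missing-data examples above it also recovered the true 12-month change.

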Semi-structured interviews will be conducted with 8–10 physiotherapists across healthcare settings (primary care, orthopaedic hospital, private practice) that have implemented the pilot programme within a five-month time-frame and those who have not implemented the programme, if appropriate. Semi-structured interviews will also be conducted with 12–15 patient participants across each setting. For people with OA, criterion purposive sampling will be used, seeking a representative sample based on sex, affected joint, disability level, duration of symptoms and number of attended sessions. The purpose of these interviews is to capture barriers and enablers to GLA:D® programme delivery and provide context related to implementation outcomes. The interview guide was adapted from Davis et al.’s [17] evaluation of GLA:D® in Canada and is presented in Additional file 4. Included topics relate to experiences providing or taking part in the programme and format (online or face-to face, if applicable), barriers or enablers encountered and any prior information or support that would have helped in delivering, taking part or adhering to the programme. Interviews will be recorded and transcribed verbatim. Interview data will be analysed thematically using a deductive approach primarily, with assistance from the CFIR codebook template for qualitative data [42, 43]. After multiple readings by the research team, codes will be assigned from units of the text and grouped into pre-defined themes using NVivo software (QSR International). Any additional themes identified using an inductive approached will be labelled as appropriate. Using reflexivity, the interviewer will also document pre-existing ideas and perspectives in an attempt to identify any biases [44]. A summary of findings from the interviews and identified themes will be presented to the steering committee to allow for additional interpretation and discussion.

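### The planned sensitivity analyses by joint site, joint replacement history and public or private setting are subgroup questions, and the one stated model gives no between-group difference

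*Protocol article*

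**What the plan says.** All the relevant text is in the protocol article, under Evaluation of effectiveness.

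- **Outcome measure.** Effectiveness is judged on "change scores (baseline to 3- or 12-month follow-up"), in a single group with no comparator, "with 95% confidence intervals to determine significance (α = 0.05) and clinical significance where a published value exists". This rule concerns change from baseline.
- **Model.** "If appropriate, a mixed-effects model will be used with patient as a random effect and time as a fixed effect". No other model is described.
- **Group comparisons.** "Sensitivity analyses will be conducted to determine differences in results related to site of pain (knee/hip), history of joint replacement" and public or private setting. The article does not say how a difference is to be estimated or tested, and it does not link this sentence to the model.

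The section on training of physiotherapists describes public and private settings as types of clinic: small and large private clinics on one side, primary care and orthopaedic hospital on the other.

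**The concern.** A sensitivity analysis asks whether one conclusion survives a change of assumption, data set or method. The sentence on group comparisons asks whether the amount of change depends on joint, surgical history or setting. That is effect modification, and it needs an estimate of the difference between groups.

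The label matters because it suggests the procedure usual for a sensitivity analysis: rerun the same analysis on a subset. With time as the only fixed effect, each rerun yields one change and one confidence interval. Two such results side by side do not answer the stated question, and they invite the reader to contrast a significant change in one group with a non-significant change in the other.

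The public or private comparison has a second difficulty. Patients of one clinic share its therapists and organisation, and a model whose only random effect is the patient treats them as independent. The Discussion stresses the two-tier health system and foresees using patient outcomes in advocacy to health authorities, so this is a result that people will look for.

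**Working it through.** The article gives no sample size, power, standard deviation or subgroup share for the effectiveness analysis. There is no figure to reproduce, and every rate below rests on stated assumptions.

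**1. What the stated model estimates.** Write it as outcome = β0 + β1·time + patient effect + error. β1 is the mean change over all patients. Fitted separately in groups A and B it gives β1A and β1B, each with its own interval. The quantity asked for is δ = β1A − β1B, with standard error √(SE_A² + SE_B²) for independent groups. Neither δ nor its standard error is a parameter of the model. With a group term and a time-by-group term, δ is the interaction coefficient.

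**2. If the significance of separate results were compared.** Suppose the true change is the same in both groups and each has power p. The chance that exactly one is significant is 2p(1 − p):

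- p = 0.80: 2 × 0.80 × 0.20 = 0.32
- p = 0.50: 2 × 0.50 × 0.50 = 0.50
- p = 0.99: 2 × 0.99 × 0.01 = 0.02

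**3. Range over assumed sizes.** For standardised change d and n patients in a group, two-sided power at 0.05 is about Φ(d√n − 1.96); the opposite tail is negligible in the rows below. With powers pA and pB, discordance is pA(1 − pB) + pB(1 − pA).

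| Total N | d | Split | pA | pB | Discordant |
|---|---|---|---|---|---|
| 100 | 0.3 | 50:50 | 0.564 | 0.564 | 0.49 |
| 100 | 0.3 | 75:25 | 0.738 | 0.323 | 0.58 |
| 200 | 0.3 | 50:50 | 0.851 | 0.851 | 0.25 |
| 200 | 0.5 | 50:50 | 0.999 | 0.999 | 0.002 |

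Over N from 50 to 500, d from 0.2 to 0.5 and both splits, the range is about 0% to 58%.

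**4. If overlap of the two intervals were used instead.** With equal standard errors SE, non-overlap requires a difference above 2 × 1.96 × SE = 3.92 SE. The standard error of the difference is √2 × SE, so z = 3.92/1.414 = 2.77 and the two-sided error is about 0.6%. This rule is too strict. The two informal rules can therefore err in opposite directions, whereas one interaction test has a 5% error rate by construction.

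**5. Price of the interaction.** With equal variance per patient, an overall change has standard error σ/√N. For a 50:50 split, δ has standard error σ√(2/N + 2/N) = 2σ/√N, so its interval is twice as wide. For 75:25 the factor is √(1/0.75 + 1/0.25) = 2.31.

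**6. Multiplicity.** Three independent interaction tests at 0.05, on one outcome at one time point, give 1 − 0.95³ = 14.3% for at least one false positive. With the four outcomes named as examples and two follow-up times there are 3 × 4 × 2 = 24 tests and 1 − 0.95²⁴ = 70.8%. That is only a rough guide, because outcomes measured on the same patients are correlated.

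**7. Clinic.** With m patients per clinic and intraclass correlation ρ of the change, the variance of a clinic-level contrast grows by a factor of about 1 + (m − 1)ρ. Neither m nor ρ is given, so only the direction can be stated: for ρ above zero, the interval from a patient-only random effect is too narrow.

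**The case against.** The best defence is that this is a condensed article and the analysis plan is not shown. The model sentence is conditional, it is not tied to the group comparisons, and nothing rules out an interaction term or a direct contrast of change scores. Effectiveness is described as monitoring beside the primary implementation outcomes. All of this is fair, and silence about an interaction term would not be a finding on its own. What stands is what the article does state: a label for the wrong kind of analysis, an aim of determining differences, and one model that cannot supply them.

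Several stronger readings are tempting, and the article does not support them.

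- **Chance differences will be reported as real.** No rule for comparing separate results is written. Depending on the rule and the sample size, the error could be far above or below 5%.
- **Leaving delivery format out of the list is an error.** Sessions "can be delivered in a face-to-face or online format, as per clinician/patient preference and capability", so a comparison by format would be confounded by self-selection. Format is taken up in the interviews, which cover "experiences providing or taking part in the programme and format (online or face-to face, if applicable"). A fourth factor would raise the figure in step 6 from 14.3% to 1 − 0.95⁴ = 18.5%. It is an optional addition.
- **Patients with both joints affected have no group.** The wording "joint problems from knee and/or hip" belongs to eligibility. The registry fields are not shown and may record an index joint.
- **A wrong public or private result would misdirect the rollout.** No passage makes the rollout depend on that contrast. Adaptation of the strategies rests on the pilot's implementation findings and the steering committee's review.

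**Conclusion.** The point holds in limited form. These comparisons are subgroup analyses under the wrong name, and the stated model does not estimate the differences they are meant to find. For the public or private contrast it also ignores the clinic.

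The size of any resulting error cannot be given. The rates of 32%, 50% and 2% assume equal true changes, equal power in independent subgroups, and a comparison of significance that the article does not prescribe. Because effectiveness is secondary here, this is an improvement worth making and not a threat to the project's main conclusions.

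**What to change.** 1. Rename these comparisons exploratory subgroup analyses.
2. For each of the three factors, add the factor and its interaction with time to the mixed model. Report the difference in change at 3 and at 12 months with its 95% confidence interval, and do not contrast the significance of separate subgroup results.
3. For public or private setting, add a clinic random effect that acts on change: either a clinic-by-time term or a clinic effect in a model of change scores. A clinic intercept alone largely cancels from within-patient change and would not widen the interval as needed.
4. State that the comparisons are unadjusted for multiplicity and give their number.

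The cost is analysis wording only. The intervals for differences will be wide, about twice that of the overall change for an even split and more once clinic is included. With few clinics the setting contrast may be too imprecise to interpret, and the report should then say so. Some chance findings must be expected, as step 6 of the working shows.
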